## Abstract

**Background:**

Mental illness is a substantial and rising contributor to the global burden of disease. Access to and utilization of mental health care, however, is limited by structural barriers such as specialist availability, time, out-of-pocket costs, and attitudinal barriers including stigma. Innovative solutions like virtual care are rapidly entering the health care domain. The advancement and adoption of virtual care for mental health, however, often occurs in the absence of rigorous evaluation and adequate planning for sustainability and spread.

**Methods:**

A pragmatic randomized controlled trial with a nested comparative effectiveness arm, and concurrent realist process evaluation to examine acceptability, effectiveness, and cost-effectiveness of the Big White Wall (BWW) online platform for mental health self-management and peer support among individuals aged 16 and older who are accessing mental health services in Ontario, Canada. Participants will be randomized to 3 months of BWW or treatment as usual. At the end of the 3 months, participants in the intervention group will have the opportunity to opt-in to an intervention extension arm. Those who opt-in will be randomized to receive an additional 3 months of BWW or no additional intervention. The primary outcome is recovery at 3 months as measured by the Recovery Assessment Scale-revised (RAS-r). Secondary outcomes include symptoms of depression and anxiety measured with the Personal Health Questionnaire-9 item (PHQ-9) and the Generalized Anxiety Disorder Questionnaire-7 item (GAD-7) respectively, quality of life measured with the EQ-5D-5L, and community integration assessed with the Community Integration Questionnaire. Cost-effectiveness evaluations will account for the cost of the intervention and direct health care costs. Qualitative interviews with participants and stakeholders will be conducted throughout.

**Discussion:**

Understanding the impact of virtual strategies, such as BWW, on patient outcomes and experience, and health system costs is essential for informing whether and how health system decision-makers can support these strategies system-wide. This requires clear evidence of effectiveness and an understanding of how the intervention works, for whom, and under what circumstances. This study will produce such effectiveness data for BWW, while simultaneously exploring the characteristics and experiences of users for whom this and similar online interventions could be helpful.

**Trial registration:**

Clinicaltrials.gov NCT02896894. Registered on 31 August 2016 (retrospectively registered).

## Background

Mental illness is a substantial and rising contributor to the global burden of disease [1]. In Canada, 1 in 5 people are affected by this leading cause of disability, associated with more than $51 billion CAD in annual costs [2]. Utilization of mental health care, however, is limited by structural barriers such as specialist availability, geography, time, out-of-pocket costs for patients [3, 4], and attitudinal barriers including stigma [4]. It is estimated that under-recognition and/or stigma act as obstacles to accessing care for at least 50 % of those affected [4–6].

Innovative solutions such as virtual care, broadly defined as any remote interaction between patients and/or health care providers using any form of information technology to enhance healthcare [7, 8], are rapidly entering the health care domain. While these innovative solutions may address some mental health care access issues through components such as anonymity and rapid availability, their advancement and adoption often occurs in the absence of rigorous evaluation and adequate planning for sustainability and spread [9].

Studies evaluating virtual mental health applications have demonstrated conflicting findings, with some trials demonstrating no benefits [10] and others demonstrating substantial improvement among participants [11]. These conflicting findings illustrate the importance of studying the processes of implementation, including contextual factors, and the mechanisms of action that help to determine whether and how virtual mental health applications have effects on patient outcomes [12]. Although a wide variety of theories and methods are available to focus attention on key issues in the adoption and scale-up of new technologies, these are only recently being applied in large implementation studies [13, 14].

In the province of Ontario, Canada, the Ontario Telemedicine Network (OTN), a non-profit and government-funded organization, is the largest provider of telemedicine services [15]. In 2015, OTN conducted a selection process to initiate a series of pilot telehomecare interventions for patients with chronic conditions, ultimately choosing to test Big White Wall (BWW) for those struggling with mental health. This manuscript describes the approach to the evaluation of this virtual mental health application within the local health care system in Ontario, Canada.

### Virtual care application: Big white wall

BWW is an internet-based application, built on evidence-based components of mental health care (eg. peer support [16], cognitive behavioural therapy [17]) combined in a virtual environment that provides anonymity (see www.bigwhitewall.com). BWW offers users access to self-assessment tools, a social network that connects people who have similar problems, and access to on-line courses. The service is monitored at all times by “Wall Guides”, trained mental health professionals (psychiatrists, social workers, and psychologists), ensuring that users are responded to and that the content posted is appropriate and safe. BWW was first developed and implemented within the National Health Service in the UK in 2007, and is now available in the UK, New Zealand, and the USA with over 35,000 users since its inception [18]. An independent pre-post evaluation of BWW users in the UK over 3 months found that 50 % showed a meaningful reduction in symptoms using validated scales of depression and anxiety [18]. While more rigorous evaluations of BWW are currently underway, it has not yet been comprehensively evaluated, and not within a Canadian context.

This protocol outlines a mixed methods study guided by a theoretical approach to examine the implementation of BWW in Ontario. The overall approach taken in this study employs a novel model of integrated knowledge translation [19], whereby the health system decision makers, implementation leads, and scientific evaluators have been engaged in the development of the research project from the outset. This approach facilitates the assessment of implementation and scalability, and increases the likelihood that results will have a future impact on health system policy.

## Methods/design

### Study aims

This study aims to evaluate whether the intervention, BWW, is acceptable, effective and cost-effective. In addition, the study aims to generate knowledge on the implementation processes and outcomes that will inform future health system decision-making regarding the potential scale-up of this and other mental health virtual care applications in Ontario.

### Hypotheses

We hypothesize that access to BWW will increase mental health recovery orientation and reduce symptoms of depression and anxiety among patients seeking specialized mental health care. Further, we expect that a greater response to BWW will be predicted by higher baseline belief in credibility and outcome expectancy of the intervention as well as actual level of engagement with the intervention. The core mechanisms by which we hypothesize BWW to be effective include: 1) enhanced self-efficacy to self-manage mental health conditions through acquisition of knowledge, personal use of tracking tools, and vicarious learning; and 2) rapid access to peer and facilitated support within a constrained health care system leading to a feeling of security and enhanced ability to cope in crisis situations.

### Study setting

This study is based in Ontario, Canada’s most populous province. In Ontario, all physician and hospital mental health care, including outpatient services located in hospitals, are publicly funded under the single-payer provincial health insurance plan [20]. Subsidized community services offer some services for free or at a low cost. [20] There is also a large network of private inter-professional health providers including social workers, psychologists and registered psychotherapists who provide counselling and psychotherapy for a fee [21]. Third party insurers may offer partial or limited coverage for these services [22]. Due to limited publicly funded services and high costs for private services, public programs have long wait times on the order of months to a year or more, and often provide time-limited treatment only [23, 24]. Although the potential for virtual mental health care platforms within this resource constrained system is apparent, few widely accessible platforms exist, and none with sufficient evidence to warrant their wide scale adoption into clinical practice.

Within Ontario, three test sites were selected from cities with populations of approximately 80,000, 150,000, and 2.5 million. These sites include: 1) a community general hospital with inpatient and outpatient mental health services and an emergency department (ED) that sees a high volume of mental health-related visits, 2) a psychiatric hospital with inpatient and outpatient mental health services, and 3) an academic ambulatory care hospital with a large outpatient mental health program. With the exception of the ED, the majority of the clinical programs accept referrals from the community or from within their respective hospital for assessment and management of chronic and/or treatment refractory mental health problems. The third site offers self-referral to some of the treatment programs with the requirement that individuals undergo an extensive intake assessment prior to being formally accepted to the waitlist.

### Participant eligibility

Eligible patients are individuals 16 years of age and older who are seeking mental health care at any of the participating sites. Inclusion criteria: 1) able to provide informed consent; 2) able to read in English; 3) able and willing to access the internet, 4) able to navigate an on-line program independently or with minimal assistance; and 5) have or are willing to obtain and use an email address. Exclusion criteria: There are no exclusion criteria but clinicians are reminded that BWW is a peer community and participants need to be able to coherently and respectfully interact with others. As such, we do not recommend individuals with severe psychosis or behavioural disorders be recruited.

### Evaluation framework

The RE-AIM framework [25] will guide the study of whether and how to scale BWW across Ontario. RE-AIM draws researchers’ attention to the issues of Reach, Effectiveness, Adoption, Implementation, and Maintenance (see Fig. 1). Within this framework, the RCT aims to evaluate reach and effectiveness, and Realist Evaluation will explore adoption, implementation and maintenance. Realist Evaluation [26] is growing in international popularity in the health services and policy research community [27], and is proposed for the evaluation of complex health care interventions [26]. Realist Evaluation has a number of appealing features for researchers and health system decision makers, as it does not simply provide a binary indication of whether an intervention works or not. Instead, it answers the question, “what works, for whom, under what circumstances” [28]?

**Fig. 1 Fig1:**
[figure not shown]
The RE-AIM Framework

### Study design

This study consists of a pragmatic randomized controlled trial (RCT) with a nested comparative effectiveness arm to assess the value of intervention extension, with concurrent Realist Evaluation. At enrollment, participants will be randomized to either immediately receive the intervention, BWW (immediate treatment group; ITG) or receive access to BWW after a 3 month waiting period (delayed treatment group; DTG). The DTG will serve as the control group during the first 3 months. After 3 months of intervention, ITG participants will have the opportunity to opt-in to an intervention extension arm. Those who opt-in will be randomized to receive an additional 3 months of BWW or no additional intervention. A purposefully sampled sub-group of trial participants, health care providers, and health system decision makers will be invited to participate in qualitative interviews throughout. The RCT study flow is depicted in Fig. 2.

**Fig. 2 Fig2:**
[figure not shown]
Detailed study flow for the RCT. ED: Emergency Department; RA: research assistant; RC: research co-ordinator; BWW: Big White Wall

### Part 1. Pragmatic randomized controlled trial

#### Recruitment

Participants will be recruited at a number of entry or exit points including outpatient clinics and their waitlists, emergency department (ED) discharges, and rapid assessment clinic discharges. Outpatient clinics include youth mental health services (age 16 and over only), adult general psychiatry consultation services (typically serving mood and anxiety disorders), psychotherapy services, post-traumatic stress and trauma therapy services, an outpatient substance use program, and a borderline personality disorder clinic. These recruitment settings were selected because: 1) they serve patients with the potential to benefit from the intervention, 2) they were identified by the participating sites and OTN as high priority settings, and 3) they have high volumes of use and turnover that will allow the implementation organization to reach their recruitment target. With the exception of the ED and rapid assessment clinics, the wait times to access these services vary from 4 months up to 2 years. Participation in the study will not affect wait list position or access to services.

Potential participants will be approached by a member of the clinical staff either by telephone, or in person in the clinic or ED. Hard-copy pamphlets or a website link to the study information will be provided. Once a potential participant indicates their interest, a research assistant (RA) or research co-ordinator (RC) will either meet them in person or contact via telephone to provide more information and obtain consent. Consent will include: 1) Consent to participate in the RCT (required), 2) Consent to be contacted for a qualitative interview (optional), 3) Consent to provide individual provincial health insurance plan (OHIP) number for linkage of survey data to health administrative data (optional), and 4) Consent for primary care provider to be notified of study enrollment (optional).

Separate consent to be re-randomized at 3 months will be obtained from ITG participants who opt-in to the nested intervention extension arm of the trial. This will be done with a question posed at the end of the 3 month data collection survey.

#### Allocation and blinding

At enrollment, a 2:1 allocation ratio will be used to randomize participants to ITG or DTG. This allocation ratio was chosen to immediately provide the intervention to more participants and increase likelihood of participation. Participants and providers will not be blind to treatment group. Randomization sequences will be generated independently and will be stratified by site and recruitment setting. Allocation sequence will be concealed until after baseline data has been collected to blind those involved in recruiting and consenting procedures. Group allocation will be revealed by phone or email. At t = 3 months, ITG participants who opt in to the nested study arm, will be randomized 1:1 to a 3 month BWW extension (ITG-e) or no extension (ITG-n). Group allocation will again be revealed via phone or email. The nested treatment extension arm will be concealed from participants at enrollment to encourage maximal usage of the intervention during the first 3 months. All data analyses will be blinded.

#### Interventions

##### Treatment as usual (months 0–3 for DTG)

Participants in the DTG will receive treatment as usual with no intervention from the study for the first 3 months. Treatment as usual may include formal or informal mental health care including pharmacological and non-pharmacological treatments. Participants recruited at discharge from clinics or the ED will receive usual recommendations regarding other services and programs that would routinely be offered upon discharge from those settings.

##### Treatment as usual + BWW (months 0–3 for ITG, months 4–6 for DTG and ITG-e)

Participants will receive a 3-month subscription to BWW, free of charge. Use of BWW is participant-driven, with the ability to utilize the services at any frequency. A unique BWW access code will be emailed to participants. If registration has not occurred within 3 days of receipt, a follow-up call will be made to remind the participant to log in. For the DTG participants, a study team member will contact them 3 months after enrollment to remind them that their access to BWW will start ﻿and the access code will be emailed. Participants randomized to ITG-e will be able to reactivate their same account once allocation has been revealed.

##### Participant safety on BWW

All participants maintain anonymity on the site through a unique non-identifiable user ID. Study participants will have a unique landing page that includes contact information for local crisis services in the event urgent assistance is required. BWW uses automated word recognition software that will alert the Wall Guides when potential safety issues are arising (eg. a user mentions ‘suicide’). The Wall Guides will then monitor that user’s activity and if deemed clinically necessary, will intervene to offer support. In the event that urgent support is required, they will direct them to use the crisis services listed on the landing page.

#### Data collection

All baseline and follow-up data will be entered into a REDCap™ database developed for the RCT. REDCap™ is confidential and is only accessible to the study personnel by secure login.

##### Baseline data

At time of consent, participants will complete a baseline questionnaire assessing socio-demographics, mental health history, measures of treatment credibility and outcome expectancy, and all outcome measures. Due to the length of time required to complete consent and all baseline questionnaires, baseline data may be collected in 1 of 3 ways depending on recruitment setting and participant preference: 1) by web survey (default); 2) by phone; or 3) in-person hard-copy.

##### Socio-demographics

Baseline data will include participant age, gender, ethnicity, education, relationship status, household income, employment status, and living situation.

##### Mental health history

At baseline, we will collect age at first onset of mental health problems, age at which formal mental health support was first sought, and duration of current episode.

##### Baseline belief in treatment credibility and outcome expectancy

Participants are asked to rate their belief in the credibility of self-help resources to improve mental health with the author-generated statement: “Self-help tools including on-line services or books are helpful for people with mental health problems” on a 4-point scale from ‘definitely agree’ to ‘completely disagree.’ In addition, they will be asked about their outcome expectancy of BWW to improve their mental health. Item #4 from the Credibility and Expectancy Questionnaire [29] will be used, “After having access to BWW for 3 months, how much improvement in your mental health do you think will occur?” Participants are asked to rate their response from 0 to 100 % with options available in 10 % increments. This single item has been shown to correlate strongly with psychotherapy outcomes [30].

##### Follow-up data (3 and 6 Months)

REDCap™ will be automated to push web-based surveys containing all outcome measures to participant emails 2 weeks prior to each pre-determined data collection time point. If, after 2 weeks, the participant has not completed the survey, a follow-up phone call will be made and confirmation of intention to complete it will be obtained and the link pushed again, or the questionnaire will be completed over the phone. For the former option, after 1 week, if still not complete a second follow-up phone call will be made and every effort to collect data over the phone will be made. All outcome measures must be completed within ±2 weeks of the intended time point.

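### Delayed-group controls may give the month-3 primary outcome after their BWW access has opened, because the code is sent by calendar and not after the survey

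*Protocol article*

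**What the plan says.** **Access.** Under Study design, "The DTG will serve as the control group during the first 3 months", and the group receives BWW once a 3-month wait is over. The Interventions section labels the BWW periods as "months 0–3 for ITG, months 4–6 for DTG and ITG-e". For the delayed group, "a study team member will contact them 3 months after enrollment to remind them that their access to BWW will start", and the code is then emailed. The same section adds a prompt to use it: "If registration has not occurred within 3 days of receipt, a follow-up call will be made to remind the participant to log in".

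**Measurement.** Under Follow-up data (3 and 6 Months), the survey is pushed "2 weeks prior to each pre-determined data collection time point". Then: "If, after 2 weeks, the participant has not completed the survey, a follow-up phone call will be made". At that call the questionnaire can be completed by telephone or the link sent again. Those who are sent the link are called once more a week later if it is still incomplete. The window is the same for both arms: "All outcome measures must be completed within ±2 weeks of the intended time point".

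**Analysis.** The primary outcome is the RAS-r total at 3 months, analysed by intent-to-treat ANCOVA. The one sensitivity analysis named under Primary and secondary analyses concerns attrition.

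**The concern.** Both timetables are anchored at month 3, and neither refers to the other. Access opens at month 3 whether or not the control has answered, while the answer is accepted for another two weeks. A late control may therefore be prompted to log in to BWW during the same days in which the unexposed measurement is being chased.

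The delayed group's month-3 value is the only control measurement in the trial, since the group then receives BWW. It feeds the primary contrast, all secondary contrasts at 3 months, the month-3 adverse-event comparison and the cost-effectiveness ratio. If BWW works, exposure among late controls narrows each outcome difference. The Limitations section already expects that a null result would be hard to interpret, and this overlap would add one more explanation for it. The people affected are not a random subset: they are those who needed chasing.

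**Working it through.** **1. Timeline, with month 3 as day 0**

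| Day | Survey (Follow-up data) | DTG access (Interventions) |
|---|---|---|
| −14 | link pushed | none |
| 0 | first call to non-responders | contact; code emailed |
| about +3 | | call if not registered |
| +7 | second call, if the link was sent again | access open |
| +14 | window closes | access open |

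The overlap is up to 14 of the 28 days in the window. Controls who have not answered by month 3 are chased at or after the point where access opens.

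**2. The same step in the other arm.** Under Recruitment, consent to re-randomization is asked at the end of the 3-month survey, so in the immediate group (ITG) assessment necessarily precedes any extension. The text gives no equivalent ordering for the delayed group.

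**3. The plan's own figure.** Inputs from Power calculation: 1000 recruited, 30% attrition, 2:1 allocation, correlation 0.8, alpha 0.05 (taken as two-sided), power 0.90, detectable difference 1.35.

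- 1000 × 0.70 = 700, which is about 233 controls and 467 treated.
- Detectable difference = (1.960 + 1.2816) × SD × √(1 − 0.8²) × √(1/233.3 + 1/466.7).
- The article gives no SD, so 1.35 cannot be reproduced independently. Solving backwards, the residual SD is 1.35 / (3.2415 × 0.0802) = 5.19 and the raw SD is 5.19 / 0.6 = 8.66.

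The dilution calculation in step 4 needs only the ratio of true to detectable difference, so it does not depend on this SD.

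**4. Dilution.** Assumptions, none of them given in the article: the true effect is 1.35; a share *f* of analysed controls answers after access opens; each has by then gained a fraction *g* of the full 3-month effect.

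- Expected difference = 1.35 × (1 − *fg*)
- Power = Φ(3.2415 × (1 − *fg*) − 1.960)

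Under linear accrual, *g* is at most 14/91 = 0.154, reached only if every late control answers on the last day. If late answers are spread evenly, mean *g* is 7/91 = 0.077. The value *g* = 0.5 stands for early benefit.

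Example: *f* = 0.5, *g* = 0.154 gives *fg* = 0.077, a difference of 1.246, and Φ(2.992 − 1.960) = Φ(1.032) = 0.849.

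| *f* | *g* = 0.077 | *g* = 0.154 | *g* = 0.5 |
|---|---|---|---|
| 0.1 | 1.34; 89.6% | 1.33; 89.1% | 1.28; 86.9% |
| 0.3 | 1.32; 88.6% | 1.29; 87.1% | 1.15; 78.7% |
| 0.5 | 1.30; 87.6% | 1.25; 84.9% | 1.01; 68.1% |

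**5. Keeping or removing late control values.** With the back-solved residual SD and complete cases only, removing a share *f* of controls gives SE = 5.19 × √(1/(233.3(1 − *f*)) + 1/466.7). Power is then 87.9%, 81.6% and 70.9% for *f* = 0.1, 0.3 and 0.5. At *f* = 0.4, removal gives 76.9%. Keeping the values gives 86.0% at *g* = 0.154, 81% at *g* = 0.3 and 73.7% at *g* = 0.5. Of these three cases, removal gains power only in the last.

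**The case against.** The strongest reply is that the order is unspecified rather than wrong. A condensed article may leave this step to the full protocol, the study-flow figure is not shown, and placing delayed access in months 4–6 suggests that measurement was meant to come first. That intention is plausible. But the two sections state specific timings, and following both to the letter produces the overlap. If the figure settles the order, the text still has to say so.

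A reader might infer that every control who needs a reminder is measured under exposure. The text does not support that. The questionnaire can be completed by telephone at the month-3 call, and nothing fixes whether that call or the access contact comes first. Holding a code is also not use: a participant must register, and the article expects that some will not have done so within 3 days. What stands is that late controls may be measured while they have access.

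A reader might also infer a large loss of power. About 62% follows if 60% of controls answer late and have half the 3-month effect within two weeks (*fg* = 0.30, difference 0.95). The documents support neither figure, and under linear accrual *g* cannot exceed 0.154. Moreover, if BWW helps, the bias is towards no difference and cannot create a false benefit.

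Finally, one might want post-access control values set to missing in the primary analysis. That would remove reluctant responders from one arm only, while late ITG values stay. It builds non-random, arm-specific missingness into an intent-to-treat analysis and can cost more power than it saves.

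**Conclusion.** The concern holds in a limited form. As written, access opens at month 3 and the control measurement is accepted until two weeks later, with no stated rule that puts the survey first. Late-responding controls may therefore give the primary outcome while they have BWW access. If BWW helps, the 3-month contrasts are biased towards no difference.

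The size cannot be determined from the article, which gives neither the share of late controls nor the speed of benefit. On linear accrual, with 10–50% late, power falls from 90% to about 89–85%. If half the benefit arrived within the overlap, the same range would be about 87–68%. The modest figures are the more likely ones. The case for acting rests on how cheaply the overlap can be removed, not on a large expected bias.

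**What to change.** - **Order.** Reconcile the Interventions and Follow-up data sections so that the DTG code email is sent only after that participant's 3-month survey is submitted or the survey window closes, whichever comes first, with the length of access unchanged. REDCap already automates the survey link and could carry this condition.
- **Dates.** Record the dates of code release, first login and survey completion for each DTG participant.
- **Analysis.** Keep all observed values in the intent-to-treat primary analysis. Prespecify a sensitivity analysis that treats DTG 3-month values dated after code release (or first login) as post-exposure, including those already collected.

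**Cost.** The change needs a database trigger, a protocol amendment and one more sensitivity analysis. Late DTG responders wait up to about two more weeks, which has to be squared with the stakeholders' requirement, noted under Limitations, on when participants receive BWW. For those participants the month-6 survey would fall up to two weeks before access ends; the randomized 6-month comparison is within the ITG and is not affected. The gate cannot protect controls whose code has already gone out. Trial status reports 475 consented, of whom about a third (475 / 3 ≈ 158) would be controls, against a minimum target of 1000, so at least 525 participants remain to be enrolled under the new rule.
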